# The recovery after Achilles tendon rupture: a protocol for a multicenter prospective cohort study

**DOI:** 10.1186/s12891-019-2437-z

**Published:** 2019-02-11

**Keywords:** Achilles tendon rupture, PROM, Ultrasound tissue characterization, Prospective cohort, Multicenter, Rehabilitation, Economic, Shared-decision making

## Abstract

**Background:**

Achilles tendon rupture (ATR) is a common sports injury, with a rising incidence and significant impairments. Due to the lack of treatment guidelines, there is no consensus about diagnostic methods, primary treatment (non-surgical or surgical) and rehabilitation. It is hypothesized that this lack of consensus and guidelines leads to sub-optimal recovery and higher societal costs.

The primary aim of this study is to give a broad insight into the recovery after ATR. Secondarily this study aims to explore factors contributing to recovery and gain insight into the cost-effectiveness of ATR management.

**Methods:**

This multicenter prospective cohort study will include all adult (≥ 18 years) patients with an ATR treated at the three main hospitals in the Northern Netherlands: University Medical Center Groningen, Martini Hospital Groningen and Medical Center Leeuwarden. All subjects will be invited for three visits at 3, 6 and 12 months post-injury. The following data will be collected: patient-reported outcome measures (PROMs), physical tests, imaging and economic questionnaires. At 3 months post-injury personal, injury, and treatment data will be collected through a baseline questionnaire and assessment of the medical file. The PROMs concern the Dutch version of the Achilles Tendon Total Rupture Score, EQ-5D-5 L, Oslo Sport Trauma Research Center Overuse Injury Questionnaire, Injury Psychological Readiness Return to Sport Scale, Tampa Scale of Kinesiophobia, Expectations, Motivation and Satisfaction questionnaire and a ranking of reasons for not returning to sport. The administered physical tests are the heel-rise test, standing dorsiflexion range of motion, resting tendon length and single leg hop for distance. Ultrasound Tissue Characterization will be used for imaging. Finally, economic data will be collected using the Productivity Cost Questionnaire and Medical Consumption Questionnaire.

**Discussion:**

This prospective cohort study will contribute to optimal decision making in the primary treatment and rehabilitation of ATRs by providing insight into (1) ATR recovery (2) novel imaging for monitoring recovery (3) (barriers to) return to sport and (4) cost-effectiveness of management. The analysis of these data strives to give a broad insight into the recovery after ATR as well as provide data on novel imaging and costs, contributing to individualized ATR management.

**Trial registration:**

Trialregister.nl. NTR6484. 20/06/2017. 20/07/2017.

Because there is conclusive evidence that outcomes after surgical and non-surgical treatment of ATRs are comparable [5], methods of rehabilitation are becoming increasingly significant [19–24]. Despite this, data on the course of the recovery after ATR are still limited, potentially resulting in suboptimal rehabilitation. Specifically, data such as psychosocial factors related to outcome (including return to sport) after ATR treatment as well as novel imaging is lacking and ATR patient continue to be burdened with a high rates of re-rupture and complications [5, 25, 26] and unpredictable recovery and return to sport (RTS) [6, 27–29]. Several patient-related (BMI, comorbidities and athletic status) and injury-related (delay in presentation, injury etiology, gap-size) factors have a possible influence on the recovery and final outcome [26, 30–35]. However, the role of these factors on ATR recovery using multiple, comprehensive outcomes has not been analyzed. Especially because the overall difference in outcome based on primary treatment (surgical or non-surgical) is minimal [5], it is important for clinicians to individualize treatment and make evidence based decisions based on specific patient and injury-related factors.

To reach this, it is essential to enhance knowledge concerning the recovery from the *patient’s perspective* (physical functioning, quality of life), the *clinical perspective* (tendon structure and strength) and *societal perspective* (costs and participation). Hence, this study aims to give a broad insight into the recovery after ATR as well as provide data on novel imaging and costs, thereby providing data that allows clinicians to individualize ATR management.

### Aims

The primary aim of this study is to give a broad insight into the recovery after ATR. Secondarily this study aims to explore factors contributing to recovery and gain insight into the cost-effectiveness of ATR management.

## Methods

### Design

A multicenter prospective cohort study will be conducted. This study has been approved by the Medical Ethical Committee (METc) of the University Medical Center Groningen (UMCG) (METc 2017/126). This study was locally approved (local feasibility) by the medical ethical committees of the Martini Hospital Groningen (MHG) (MEC 2017–087) and Medical Center Leeuwarden (MCL) (COV 274(a)).

### Participants and setting

Eligible patients are all patients with an ATR who are treated at the three largest hospitals in the Northern Netherlands: UMCG, MHG and/or MCL. Patients will be included within the first 3 months post-injury.

*Inclusion criteria:*
Older than 18 years of age at the time of inclusionClinically diagnosed with an ATR and treated at the UMCG, MHG and/or MCL

*Exclusion criteria:*
Unable to understand written DutchPhysically unable to perform the tests and/or cognitively unable to complete the questionnaires

### Sample size calculation

A formal sample size calculation is difficult due to the exploratory design of this cohort study as well as the lack of comparable data on ATR recovery. All eligible patients within the designated inclusion period who consent to participate will be included. Based on hospital data indicating the treatment of approximately 15 ATRs per hospital per year as well as similar studies by the research group showing a dropout of 10–20%, we estimate 50 patients will be included. This number will allow us to include at least 5 independent variables in the regression analyses based on “the rule of thumb” of 10 subjects per variable (one in ten rule) [36–38]. Other studies assessing ATR recovery usually included lower patient numbers [20, 27, 39, 40].

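### Fifty patients at ten subjects per variable allow at most five regression variables, not at least five, and only four if the stated dropout is still to come off the 50

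*Protocol article*

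**What the plan says.** The Sample size calculation section of the protocol article offers no formal calculation, because the study is exploratory and comparable data are scarce. It sets the size by accrual: "All eligible patients within the designated inclusion period who consent to participate will be included". The expected number rests on two inputs, the "treatment of approximately 15 ATRs per hospital per year as well as similar studies by the research group showing a dropout" of 10 to 20 percent, and the result is "we estimate 50 patients will be included". The length of the inclusion period is not given there.

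The section then says what this number permits: "This number will allow us to include at least 5 independent variables in the regression analyses". The yardstick is a rule of thumb of "10 subjects per variable (one in ten rule").

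The number of hospitals comes from Participants and setting, where patients are those "treated at the three largest hospitals in the Northern Netherlands: UMCG, MHG and/or MCL". The same section places inclusion within three months of injury, and Data collection sets visits at 3, 6 and 12 months.

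Under Statistical analysis, the secondary aim uses linear regression of the ATRS-NL score, with no visit named for the outcome. Each factor is tested singly, and every factor with p below 0.20 enters the multiple model. No maximum number of factors is stated.

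**The concern.** A subjects-per-variable rule limits how large a model may be. The article presents that limit as a guaranteed minimum, which suggests there is room above five when the rule leaves none.

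The wording matters because this is the only quantitative statement of what the sample can support, and because the selection step under Statistical analysis has no limit of its own. Demographic and lifestyle data alone lists age, height, weight, smoking, physical activity, work, and urban or rural residence, which is seven candidates. Medical data adds gap size, treatment delay, type of treatment and others. With p < 0.20 as the only entry criterion, more than five factors could enter the model, and the words meant to justify the sample size would not stand in the way.

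A second question is whether the rule has been applied to the right number of patients. The 10 to 20 percent dropout is cited, but the text does not settle whether it has already been taken off the 50.

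**Working it through.** **Inputs** (Sample size calculation unless noted)
- Ruptures treated per hospital per year: 15, taken at face value
- Hospitals: 3 (Participants and setting)
- Dropout, d: 0.10 to 0.20
- Patients expected: 50
- Subjects per variable: 10
- Length of inclusion: not given

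**Step 1. The plan's own figure.** Variables allowed = N/10, rounded down. With N = 50, 50/10 = 5. The number five is reproduced, but as a maximum. A sixth variable would need 60 patients.

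**Step 2. If 50 is the number enrolled.** Patients with complete follow-up = 50 × (1 − d).
- d = 0.10: 50 × 0.90 = 45, and 45/10 = 4.5, so 4 variables
- d = 0.20: 50 × 0.80 = 40, and 40/10 = 4.0, so 4 variables

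Five variables would then have 45/5 = 9 or 40/5 = 8 subjects each, below the stated ten.

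**Step 3. If 50 is already net of dropout.** The limit stays at 5. Enrolment must then be 50/(1 − d).
- d = 0.10: 50/0.90 = 55.6, so 56 patients
- d = 0.20: 50/0.80 = 62.5, so 63 patients

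**Step 4. Is 50 attainable from the stated rate?** 3 × 15 = 45 ruptures per year. Months needed = 12 × (number to enrol)/45, if every patient is eligible and consents.
- 50 enrolled: 12 × 50/45 = 13.3 months
- 50 after 10% dropout: 12 × 55.6/45 = 14.8 months
- 50 after 20% dropout: 12 × 62.5/45 = 16.7 months

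| Meaning of 50 | To enrol | Left after dropout | Most variables at 10 each | Shortest inclusion |
|---|---|---|---|---|
| Enrolled | 50 | 40 to 45 | 4 | 13.3 months |
| Net of dropout | 56 to 63 | 50 | 5 | 14.8 to 16.7 months |

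Neither row supports five as a minimum.

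**Step 5. Which meaning does the text favour?** The sentence before the estimate ties inclusion to eligibility and consent, and Participants and setting puts it within three months of injury. That is enrolment, so 50 would be before dropout. Against this, the dropout rate is named as one of the grounds for the 50, which suggests it has already been taken off. The wording leans towards the first meaning but does not settle it.

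**The case against.** The strongest defence is that the 50 is described as an estimate, that size is fixed by accrual, and that the ten-per-variable remark is a rule of thumb in an exploratory study. If 50 is net of dropout, five variables is exactly what the rule gives, and the remedy is a change of phrase. Most of this stands. It keeps the point modest, but it does not rescue the phrase, because on the reading most favourable to the article five is still the maximum.

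Stronger readings are tempting, and the document does not support them.

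- A reader might infer that 50 is contradicted, because 45 per year less 10 to 20 percent leaves 36 to 40.5. That holds per 12 months only. The article gives a yearly rate and an inclusion period whose length is not stated, and about 15 to 17 months at full consent yields 50 net. A condensed article may leave the length of accrual to the full protocol.
- A reader might notice that 45/0.9 is exactly 50 and infer that dropout was applied in the wrong direction to a one-year count. The article does not show how it reached 50, so this cannot be attributed to it.
- A reader might conclude that the limit is four outright. That holds only if 50 is the number enrolled and the outcome is taken after the stated losses.
- A reader might say that the 12-month model is over-parameterised. The article names no visit for the regression outcome and fixes no number of predictors, so this is not shown. At an earlier visit fewer patients may have been lost, but the limit still could not exceed five.

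**Conclusion.** The point holds in this form: the article states an upper limit as a lower one. At ten subjects per variable, 50 patients support at most five variables, with no assumption needed about consent, dropout or length of inclusion. If 50 is the number enrolled, as the wording rather suggests, and the full 10 to 20 percent has been lost by the visit analysed, the limit is four.

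The size is small, one or two variables, and no patient number is shown to be wrong. The 50 is compatible with the stated rate, but implies more than one year of inclusion: at least 13.3 months before dropout, or 14.8 to 16.7 months after it. These are minimum durations, since they assume that every treated patient is eligible and consents. The correction is worth making because the p < 0.20 entry step has no other bound.

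**What to change.** 1. In Sample size calculation, say whether 50 is before or after dropout, and give the number of patients expected at the visit whose ATRS-NL score is the regression outcome.
2. Replace the claim of a minimum of five variables with: at most five parameters, or at most four if 50 is the number enrolled and the outcome is taken after the stated dropout. Count each dummy variable of a categorical factor as a parameter.
3. In Statistical analysis, apply that limit as a cap on the multiple linear regression, so that the p < 0.20 step cannot admit more parameters than the article's own rule allows.

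The cost is rewording and a slightly less favourable figure. No extra patients or measurements are needed.

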### Statistical analysis

IBM SPSS Statistics for Windows software (Version 23.0, Armonk, NY: IBM Corp.) will be used for all statistical data analyses. Descriptive statistics (frequencies, means and standard deviations, etc.) will be used to describe all data. Spearman’s correlation coefficients will be used to describe association between data. Statistical significance is defined as *P* < 0.05.

The following are the planned statistical analyses *per aim*:
*Primary aim:*
Generalized estimating equations (GEEs) will be conducted to assess the outcomes over time: 3, 6, and 12 months.

*Secondary aim:*
Linear regression analyses will be performed to assess factors predictive of Achilles tendon function. First, univariate analysis will be performed as a hypothesis-generating analysis model with ATRS-NL score (0–100) as dependent variable and a predicting factor as independent factor. Factors showing a relation with the outcome measure with a *p*-value < 0.20 will be included in a multiple linear regression analysis. Additionally, binary logistic regression will be used to determine the factors associated with returning to the pre-injury sport or recreational activity. Return to the pre-injury activity (yes or no) is the outcome variable.The Incremental Cost-effectiveness Ratio (ICER) (=Δ Cost of treatment/Δ Effect of treatment) associated with each unique treatment modality will be calculated. The ICER is calculated by taking the difference in costs associated with each possible treatment modality and its alternative (e.g. physiotherapy vs. no physiotherapy) and dividing by the difference in effect. Costs are calculated by adding the direct (e.g. cost of treatment from iMCQ questionnaire) and indirect (e.g. loss of work, from iPCQ questionnaire) costs associated with each possible treatment. Effect consists of the EQ-5D-5 L and/or ATRS-NL outcomes. The cost-effectiveness of ATR management options will herewith be determined at 3, 6, and 12 months post injury.

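### The claim that 50 patients support at least five predictors fits the linear model but not the logistic return-to-activity model, where the same rule supports at most two

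*Protocol article*

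**What the plan says.** The Sample size calculation section of the protocol article explains that a formal calculation is difficult in an exploratory cohort. It then gives an expected number, "we estimate 50 patients will be included", based on "approximately 15 ATRs per hospital per year" and on "similar studies by the research group showing a dropout of 10–20" per cent. The number is supported by one quantitative statement: "This number will allow us to include at least 5 independent variables in the regression analyses", on the basis of "10 subjects per variable (one in ten rule". The sentence does not distinguish between types of regression.

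The Statistical analysis section, under the secondary aim, plans two types. The first is linear: "Linear regression analyses will be performed to assess factors predictive of Achilles tendon function", with the ATRS-NL score as dependent variable, univariate screening at p < 0.20, and then a multiple linear model. The second is logistic: "binary logistic regression will be used to determine the factors associated with returning to the pre-injury sport or recreational activity". Its outcome is binary: "Return to the pre-injury activity (yes or no) is the outcome variable". The article gives no expected return rate and no number of predictors for the logistic model.

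**The concern.** The plan applies one count, total patients divided by ten, to regressions on two different kinds of outcome. For a continuous score every analysed patient adds information, so counting subjects is reasonable. For a yes/no outcome the information is limited by the less frequent answer. In the extreme, if all 50 patients returned to their activity, no predictor effect could be estimated, although the subject count would still be 50. This is why the one-in-ten rule, applied to logistic regression, counts patients in the smaller outcome group.

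At stake is the size of the logistic model. The Background names six candidate patient and injury factors (BMI, comorbidities, athletic status, presentation delay, etiology, gap size), and the baseline questionnaire and medical file add more. An analyst who takes the sample size section at its word could enter five of them. That would invite overfitting, with unstable or inflated odds ratios and possibly separation.

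**Working it through.** **Inputs.** From the Sample size calculation section: N = 50 patients, 10 per variable, 5 variables claimed, dropout 10–20%. From the Statistical analysis section: one continuous outcome (ATRS-NL) and one binary outcome (return, yes or no). The return rate is not given, so the share of patients in the smaller outcome group, p, is an assumption wherever a value below its ceiling of 0.5 is used.

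**Step 1: the plan's own figure.** N/10 = 50/10 = 5. The figure is reproduced, and it is a valid count for the linear model if all 50 are analysed.

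**Step 2: ceiling for the logistic model.** The number of variables is N × p / 10, with p at most 0.5. The smaller group is at most 50 × 0.5 = 25, so the ceiling is 25/10 = 2.5, or two whole variables. This step needs no assumed return rate.

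**Step 3: uneven splits (assumed shares, N = 50).**

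| Share in smaller group | Patients in it | Variables at 10 each | Patients in it per variable, if 5 entered |
|---|---|---|---|
| 50% (ceiling) | 25 | 2.5 | 5 |
| 40% | 20 | 2.0 | 4 |
| 30% | 15 | 1.5 | 3 |
| 20% | 10 | 1.0 | 2 |

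**Step 4: what five variables would need.** The smaller group must hold 5 × 10 = 50 patients, so N = 50/p: 100 patients at an even split, and 125, 167 and 250 at shares of 40%, 30% and 20%.

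**Step 5: sensitivity to dropout.** The article does not say outright whether 50 is before or after dropout. If it were before, 50 × 0.9 = 45 or 50 × 0.8 = 40 patients would be analysed. The logistic ceiling would be 45 × 0.5 / 10 = 2.25 or 40 × 0.5 / 10 = 2.0, still two variables. The conclusion does not depend on this question.

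**The case against.** The strongest reply is that the five-variable sentence was meant only for the linear model. That model alone has a described multivariable build, and the logistic regression is introduced afterwards as an addition. This reading is possible, but the sentence is plural and unqualified, and the plan contains two kinds of regression. If the linear model alone was meant, the text still has to say so.

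A second reply is that ten per variable is only a rule of thumb and the study is exploratory. Both are true and both limit the severity. They do not rescue the statement, because the plan chose this rule as its support and the rule gives a different answer for a binary outcome.

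Four stronger readings are tempting, and the documents do not support them:

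- A reader might infer that the cohort supports one to two variables as an established range. Only the upper limit of two is established; the lower figures rest on assumed return rates.
- A reader might deduct 10–20% dropout from 50. The section cites dropout among the grounds for reaching 50, so a further deduction may count it twice.
- A reader might infer that a five-variable logistic model is planned. The Statistical analysis section fixes no number of predictors for it. The overfitting is a risk that the capacity statement opens up, and its size has not been calculated here.
- A reader might conclude that the study's contribution on barriers to resuming sport fails. That topic is also served by the ranking of reasons for not returning and by the I-PRRS, TSK and modified OSTRC questionnaires.

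**Conclusion.** The point holds for the logistic model. Five variables cannot be reconciled with the plan's own rule for that model at any return rate: the limit is two at best, and five variables would have at most 5 patients in the smaller group each, against the 10 the plan relies on. This rests on two things only: 50 analysed patients, as the article expects, and the standard counting of the rule by the smaller outcome group.

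The division is correct, and the count is suitable for the linear ATRS-NL model if all 50 are analysed. The primary aim is analysed by GEE and is untouched. Enrolment does not change either, because all eligible consenting patients in the inclusion period are taken. The logistic regression is an additional analysis under a secondary, exploratory aim. The severity is therefore moderate: a stated property of the design needs correcting, but the study is not undermined.

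**What to change.** In the Sample size calculation section, restrict the five-variable statement to the linear regression on ATRS-NL. Add a separate sentence for the logistic regression, for example: the number of variables will not exceed the number of patients in the smaller return group divided by 10, which is at most two with 50 patients. If more variables are to be entered, state that a penalised logistic model (for example Firth) will be used and reported as exploratory. The choice of the individual predictors can be left to the analysis plan.

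The cost is a change of wording, a less favourable stated capacity, and a shorter or penalised logistic model. No extra patients or data are needed.

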### Study procedures

#### Recruitment

The conducting researcher ([name]) will screen the list of patients treated at the Emergency Departments of the UMCG, MHG or MCL and contact all who have been treated for an ATR. All subjects will receive oral and written information about the study prior to giving informed consent.

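### Recruitment names only Emergency Department lists for finding cases, although the cohort is defined as all adults with an ATR treated at the three hospitals

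*Protocol article*

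**What the plan says.** Four places in the protocol article describe whom the study covers, and all define the population by treatment at a hospital.

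- **Abstract, Methods:** the study "will include all adult (≥ 18 years) patients with an ATR treated at the three main hospitals in the Northern Netherlands".
- **Participants and setting:** the eligible group is given as "Eligible patients are all patients with an ATR who are treated at the three largest hospitals in the Northern Netherlands". The inclusion criterion repeats treatment at these hospitals and does not mention the Emergency Department (ED). The same section adds a time limit: "Patients will be included within the first 3 months post-injury".
- **Sample size calculation, coverage:** "All eligible patients within the designated inclusion period who consent to participate will be included".
- **Sample size calculation, accrual:** the expected number of 50 rests on "hospital data indicating the treatment of approximately 15 ATRs per hospital per year", which is a count of treated ruptures.

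One place says how patients are found. Under **Recruitment**, the researcher "will screen the list of patients treated at the Emergency Departments of the UMCG, MHG or MCL" and contacts those on it who were treated for an ATR. No second source is named.

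On delay, the **Background** lists among injury-related factors that may influence recovery: "delay in presentation, injury etiology, gap-size". **Medical data** includes treatment delay among the items taken from the patient's file. **Statistical analysis** does not list the predictors for the regressions.

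**The concern.** The list from which patients are drawn is narrower than the population that the results are meant to describe. A patient treated at one of the hospitals who never passed through its ED meets every eligibility criterion, yet does not appear on the only list that is screened.

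This matters for two reasons. The primary aim is a broad description of recovery, so who enters the cohort largely determines what the description means. And a patient who is never listed cannot be counted: a report built on ED lists could not say how many eligible patients were missed or how they differed from those included.

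There is also a possible link to a factor of interest. If entry route is related to delay in presentation, the ED lists would select partly on a variable that the study names and collects.

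**Working it through.** **1. Population against screening source.**

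| Place in the article | Defined by | ED required? |
|---|---|---|
| Abstract, Methods | treatment at one of the three hospitals | no |
| Participants and setting | treatment at one of the three hospitals, inclusion within 3 months of injury | no |
| Sample size calculation | all eligible and consenting; accrual from treated ruptures | no |
| Recruitment | presence on an ED list | yes |

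The first three agree with each other. The fourth is a subset of them, and equals them only if every treated patient passes through the ED. The article does not say that this is so.

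**2. The plan's own figures.** Inputs from Sample size calculation: 15 ruptures per hospital per year, 10–20% dropout, 50 patients, 10 subjects per variable. Three hospitals come from Participants and setting.

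- Treated ruptures per year: 3 × 15 = 45.
- Variables supported: 50 / 10 = 5, as stated.
- Years needed for 50, T = 50 / [45 × (1 − d)] with d the dropout: 1.11 at d = 0, 1.23 at d = 10%, 1.39 at d = 20%.

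The length of the inclusion period is not given, so 50 can be neither confirmed nor refuted.

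**3. Effect of screening ED lists alone.** Let f be the share of treated patients who are on no ED list. The article gives no value, so 0–20% is assumed. The number found is 50 × (1 − f).

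| Assumed f | Patients | Patients / 10 |
|---|---|---|
| 0% | 50 | 5.0 |
| 5% | 47.5 | 4.75 |
| 10% | 45 | 4.5 |
| 20% | 40 | 4.0 |

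This takes the 15 per hospital as a count of all treated ruptures, as the text says. If those hospital data were themselves drawn from ED records, the 50 would already be an ED figure and this loss would not apply. The mismatch in step 1 would remain.

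A longer inclusion period could restore the number. At f = 20%, T = 50 / [45 × 0.8 × (1 − d)], which is 1.54 years at 10% dropout and 1.74 at 20%. It would not restore coverage, because the same routes would still go unscreened.

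**4. Delay.** A figure for the effect on the delay variable needs the share bypassing the ED and the distribution of delay in each group. The article gives none of these, so no figure is offered.

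**The case against.** The strongest reply is that Recruitment is a two-sentence paragraph in a journal article. It does not say that ED lists are the sole source, and the full ethics-approved protocol, which is not shown, may name others. The Background describes a rupture as an acute event with severe pain and inability to bear weight, which fits ED entry as the norm. If almost everyone enters that way, almost nothing is lost.

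Part of this stands. That the source is exclusive is inferred from no other being named, and the bypass share may be close to zero. But the article is not silent on case finding. It states a source, and that source is narrower than the population stated elsewhere in the same article. This is a mismatch between two statements, not a detail left out.

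A reader might go further and infer that the patients missed are chiefly late presenters, that the range of delay is cut off, and that the regression therefore cannot estimate an effect of delay. The article does not support this. It does not say who bypasses the ED or when they present. A late presenter seen at an ED stays on the list, so long delays would at most be thinned. The one explicit limit related to delay is the 3-month inclusion window, which is a separate matter. Delay is also only a possible candidate predictor, since the analysis section names none. Any multiple for the loss of precision would depend almost entirely on assumed standard deviations of delay.

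**Conclusion.** The point holds as a mismatch between population and screening source. Followed as written, Recruitment would not find an eligible patient who was treated at one of the hospitals without passing through its ED, and the report could not say how many such patients there were. This conclusion needs no assumption beyond reading the ED lists as the one source named.

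The size is uncertain. Under an assumed bypass share of 0–20%, 50 patients become 50 to 40, and the rule of ten supports 5 to 4 variables. At 0% nothing is lost. Under-representation of long delays is possible if entry route and delay are related; its extent cannot be derived from the article. The change is still worth making, because it is cheap and because it would show whether the claim to cover all patients is justified.

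**What to change.** In Recruitment, have the same researcher also query the ATR diagnosis code at each hospital (or, failing that, the outpatient and operating lists), keeping the 3-month inclusion window. Record the entry route for each patient, and report the numbers eligible, approached and included by route.

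If this cannot be done, restate the population in the Abstract and in Participants and setting as patients treated through the Emergency Department, and bring the coverage statement in Sample size calculation into line.

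The cost is one further query per hospital by someone who already screens, slightly more screening time, and a change of wording. If nearly all patients turn out to enter through the ED, the query will show it and the present description of the cohort can stand.
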